## Methods

### Overview of study design

This is a single centre, open-label randomised controlled feasibility study with a nested qualitative component. Feasibility will be determined by assessing recruitment, adherence to the intervention and retention rates. Acceptability and patient experience will be assessed through patient-reported outcome (PRO) questionnaires, and an optional nested qualitative study consisting of either focus groups or semistructured telephone interviews if insufficient numbers can be recruited to form focus groups.

Fifty participants will be randomised (via a computer-generated programme) in a 1:1 ratio to the intervention or standard care for this population (figure 1 study flow). The randomisation will be minimised by age (<65 vs ≥65 years). Participants randomised to the intervention arm will complete eight supervised (one per week) and 12 telephone coaching sessions over 12 weeks. Outcomes will be assessed at baseline, 12, 24 and 52 weeks from the first exercise session for those in the intervention group and from randomisation for those in the standard care group.

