### Sample size

This is a feasibility study, and therefore a formal sample size calculation has not been performed. The study is not designed or powered to detect a statistically significant difference in efficacy between the two treatment arms.

A pragmatic recruitment target of 50 participants has been chosen as we expect this number will be feasible within a single centre with a population of 250 patients and should be sufficient to provide estimates of the feasibility outcomes. A sample size of between 24 and 50 is recommended for pilot studies to estimate sample sizes for a full trial.^20^

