### Study procedures

The study outcomes, measurement methods and assessments are summarised in table 1. Data are collected at baseline, and then at 12, 24 and 52 weeks, from the first exercise session for those in the intervention group and from randomisation for those in the standard care group. Data on recruitment, number of activity sessions and telephone coaching sessions completed and drop outs will also be recorded.

**Table 1 T1:** Visit overview

Visit	Prebaseline	Baseline	Baseline (+4 weeks)	Weeks 1–8	Weeks 9–12	Week 12*	Week 24*	†Week 52*
Identification of eligible patients	x							
Eligibility check	x	x						
Valid informed consent		x						
Relevant medical history taken		x						
Randomisation (without patient present)			x					
Activity advice telephone call (control arm only)‡				x				
Exercise visits (intervention arm only)				x				
Weekly telephone coaching contacts (intervention arm only)				x	x			
Follow-up clinic visits*§						x	x	
Final assessment (postal questionnaires)*§								x
Quality of life questionnaires		x				x	x	x
Focus groups or interviews (postintervention)					x	x	x	

*The timing of the follow-up visits for intervention group are taken from intervention start date, not randomisation date; for the control group, the timing is taken from randomisation date.

†52 weeks follow-up assessment can be completed—2 weeks before due date and up to 8 weeks after the due date.

‡Control group have one telephone call in week 1 (postrandomisation) to receive standard activity advice only.

§12-week and 24-week follow-up assessments can be completed up to—2 weeks before due date and up to 3 weeks after the due date.

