### Study outcomes and data analysis

The primary outcome of this feasibility trial is to determine if a full RCT comparing physical activity with behaviour change support versus standard care in patients with AAV is feasible. This decision will be made using a composite assessment of both quantitative and qualitative data based on a traffic light system using predefined stop-go criteria. The three criteria contributing to the traffic light system include^1^ recruitment rates, defined as the proportion of eligible patients recruited into the study^2^; successful adherence to the intervention, defined as attendance at a minimum of 4 of the 8 visits for the face to face support, and acceptance of a minimum of 3 of the 4 telephone support calls in weeks 9–12 and^3^ study drop-out, defined as complete withdrawal from the study, with no further data collected from the participant. The traffic light system comprises (1) green light: recruitment rate >50%; adherence rate >75% and drop-out rate <15% excluding those patients who drop-out or are unable to achieve adherence due to disease activity. If all three criteria are met, we will proceed to a full trial with the protocol unchanged (unless there is a clear message from the qualitative work that would improve the protocol). (2) Amber light: recruitment rate 30%–50%, adherence rate 50%–75% or drop-out rate 15%–30% excluding those patients who drop-out or are unable to achieve adherence due to disease activity. If one or more of our amber light criteria are met, we will adapt the protocol in light of the result of the feedback from the qualitative work and our experience to improve whichever criteria are not at the ‘green-light’ level before proceeding to full trial if possible. We will assess whether adaption of the protocol will require a further feasibility study or pilot study before progressing. (3) Red light: recruitment rate <30%, adherence rate <50% or drop-out rate >30% excluding those patients who drop-out or are unable to achieve adherence for disease activity. If one or more of these criteria are met we would consider the current protocol not feasible and not progress to a full RCT.

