The primary analysis to assess the stop-go criteria will be undertaken once all participants have completed the 24-week assessment, and corresponding outcome data has been entered onto the study database and validated as being ready for analysis. Feasibility outcomes including the three components of the stop-go criteria will be analysed by pooling the two randomised groups and presenting overall estimates with 95% CI. Reasons for non-entry into the trial will be assessed, particularly in relation to the patient eligibility criteria and reasons for patient refusal. Data on patients who stop the intervention and/or who do not complete the trial (such as withdrawals and those lost to follow-up) will be collected throughout the trial to allow assessment of patient adherence and retention rates. Reasons for non-adherence and non-completion will be analysed descriptively.

All clinical and patient-reported outcomes will primarily take the form of simple descriptive statistics (eg, proportions and percentages, means and SD) and where appropriate, point estimates of effects sizes (eg, mean differences and relative risks) and associated 95% CI. Data return rates at each time point will be assessed along with data completeness of the various outcomes measures. This will inform the use of appropriate questionnaires for the primary outcome in a future study. The data will be analysed using the intention to treat principle, where patients are analysed in the treatment group to which they were randomised regardless of adherence to intervention or compliance with the protocol.

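### The protocol pools both arms for all three stop-go components, but adherence is defined only in the intervention arm, so a pooled adherence rate cannot be meaningfully judged against its thresholds

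*Protocol article*

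**What the plan says.** All statements are in the Protocol article.

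- **Analysis population** (Study outcomes and data analysis): "Feasibility outcomes including the three components of the stop-go criteria will be analysed by pooling the two randomised groups", with the results given by "presenting overall estimates with 95% CI". No component is excepted.
- **Definition of adherence** (same section): "successful adherence to the intervention, defined as attendance at a minimum of 4 of the 8 visits for the face to face support", together with "acceptance of a minimum of 3 of the 4 telephone support calls in weeks 9–12".
- **Thresholds** (same section): adherence is green above 75%, amber from 50% to 75% and red below 50%. Patients who cannot adhere because of disease activity are left out. Any single red criterion means the full trial does not go ahead.
- **Who is offered what** (Study procedures, Table 1): the rows read "Exercise visits (intervention arm only" and "Weekly telephone coaching contacts (intervention arm only", each closing its bracket there. A footnote gives the control group one advice call in week 1 and nothing more.
- **Size** (Overview of study design): "Fifty participants will be randomised (via a computer-generated programme) in a 1:1 ratio to the intervention or standard care for this population".

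Nowhere does the article restrict the adherence denominator to the intervention arm.

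**The concern.** Half of the pooled sample is offered neither the visits nor the calls that define adherence. Those participants can neither succeed nor fail, so a proportion taken over both arms does not estimate adherence to the programme.

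The thresholds make sense as statements about people given the programme. Applied to a pooled figure, they judge a different quantity, whose value depends on an unstated convention for scoring controls. Adherence is one of three criteria that decide the primary outcome. Pre-specified stop-go criteria are meant to remove such discretion, and here the same intervention-arm data could produce different lights.

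**Working it through.** There is no planned figure to reproduce. The article says "This is a feasibility study, and therefore a formal sample size calculation has not been performed", and it gives no expected adherence rate.

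**Inputs.** 50 participants at 1:1, taken as 25 per arm (Overview of study design); thresholds of 75% and 50% (Study outcomes and data analysis). Assumptions: exactly 25 per arm and nobody excluded for disease activity. True adherence rates of 80%, 90% and 95% are illustrative. Let x be the number adherent among the 25 in the intervention arm.

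**Step 1: intervention arm only, rate = x/25.**
- Green needs x > 0.75 × 25 = 18.75, so at least 19/25 = 76%.
- Amber is 13 to 18 (52% to 72%).
- Red is 12 or fewer (48% or less).
- With true adherence of 80%, the binomial distribution gives P(green) = 0.78 and P(red) = 0.0004. With 90%, P(green) = 0.99.

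**Step 2: both arms, controls scored non-adherent, rate = x/50.**
- The maximum is 25/50 = 50%, so green cannot occur and amber needs 25/25.
- One non-adherer gives 24/50 = 48%, red. Hence P(red) = 1 − p^25:

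| True adherence p | P(red), pooled |
|---|---|
| 0.80 | 1 − 0.80^25 = 0.996 |
| 0.90 | 1 − 0.90^25 = 0.93 |
| 0.95 | 1 − 0.95^25 = 0.72 |

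- 19/25 (76%, green on its own arm) becomes 19/50 = 38%, red.
- Sensitivity to the arm split: with 23 to 27 of the 50 in the intervention arm, the ceiling is 46% to 54%, still far below green.
- Sensitivity to exclusions: one intervention participant removed for disease activity puts perfect adherence at 24/49 = 49%, red.

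**Step 3: both arms, controls scored adherent, rate = (x + 25)/50.**
- 13/25 (52%, amber) becomes 38/50 = 76%, green.
- The lowest possible value is 25/50 = 50% at x = 0, so red cannot occur.
- The exact 95% CI for 38/50 is 62% to 87%. For the 13/25 behind it, the interval is 31% to 72%.

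**Step 4: controls contribute no observation.** The overall estimate is then x/25, as in step 1. This gives a sensible answer, but nothing has been pooled.

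**The case against.** The strongest reply is that the intended denominator is plain. The criterion concerns adherence to the intervention, the disease-activity exclusion fits only people who had something to adhere to, and the pooling sentence cannot be literal for recruitment either, since that rate includes eligible patients who were never randomised. Read this way, pooling is shorthand for giving overall estimates without comparing arms. As a guide to intent this stands, and the authors probably did mean the intervention arm.

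It follows that a stronger reading fails. A reader might infer that green is unreachable under this plan and that a well-adhered programme would certainly be stopped. The article does not support that: it never says controls are scored as non-adherers, and the 50% ceiling and the P(red) values hold only under that scoring.

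The objection does not make the sentence right, because it names the three components together and an analyst would follow it. Three further replies do not rescue it:

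- **A separate analysis plan could settle the matter.** This is not an omitted detail. The article fixes a population that conflicts with its own definition, so a plan using one arm would contradict it.
- **Intention to treat.** That principle keeps patients in their randomised group. It does not create adherence data for people offered no sessions.
- **The decision also uses qualitative data.** The article gives that work a role under green and amber, but describes none in overriding red.

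**Conclusion.** Wrong as written. The pooling rule contradicts the definition of adherence and Table 1, and it governs a primary go/no-go criterion. The error is specific to adherence: pooling is workable for drop-out, and recruitment is settled before randomisation.

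How far the result moves depends on the unstated scoring of controls. Scored as non-adherent, they turn a result that is green on its own arm into red. Scored as adherent, they lift a result in the low 50s to green and remove red altogether. Left out, they cause no harm. The figures rest on 25 per arm and no disease-activity exclusions. The contradiction itself rests on neither.

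**What to change.** In Study outcomes and data analysis, replace the pooling sentence with one that gives a denominator for each component, for example:

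> Adherence will be estimated only in participants randomised to the intervention, after the disease-activity exclusions specified for the stop-go criteria, with an exact 95% CI. Recruitment will be estimated with eligible patients as the denominator, as already defined. Drop-out will be estimated over both randomised groups combined, with the same exclusions.

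The recruitment denominator should stay at eligible patients. Changing it to all those screened would alter the meaning of the 50% and 30% thresholds.

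The change is to wording only: no extra data, no extra participants and no new thresholds. The price is precision. With about 25 participants, an observed 19/25 has an exact 95% CI of 55% to 91%, which reaches from amber well into green. That is the precision the design actually offers for adherence.

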## Aims and objectives

The aim of this study is to assess the feasibility and acceptability of undertaking a phase III randomised controlled trial (RCT) of physical activity with behaviour change support including device assisted self-monitoring and telephone support with cognitive behavioural strategies compared with standard of care in patients with AAV.

The specific objectives of the study are to:Assess different recruitment methods to the trial for example, where and how patients are identified and recruited.Assess recruitment and retention rates in the trial.Assess the acceptability of the intervention and the burden of trial participation on patients.Assess adherence to the trial intervention.Assess the safety of the intervention with respect to possible injury and deterioration in fatigue levels as a result of participating in a physical activity trial.Assess the effect of trial participation on activity levels in patients in the standard care group.Test procedures for the trial, including delivery of the standardised protocolled intervention and administration of trial questionnaires and other outcome measurement tools, and identify areas that may improve the design and implementation of the intervention.Collect data on the variability of the outcome measures to inform a power calculation for a definitive trial.Provide an estimate of the cost of implementing the intervention.Collect feedback from patients on their experience of participating in the study.

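### Drop-out enters the stop-go decision only as a pooled rate, so an intervention arm at amber level can read as green on that criterion and differential attrition is not quantified

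*Protocol article*

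**What the plan says.** All references are to the Protocol article.

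- **Drop-out** (Study outcomes and data analysis) is "study drop-out, defined as complete withdrawal from the study, with no further data collected from the participant".
- **Bands** (same section). Green is "drop-out rate <15% excluding those patients who drop-out or are unable to achieve adherence due to disease activity". Amber is "drop-out rate 15%–30% excluding those patients who drop-out or are unable to achieve adherence due to disease activity". Red is above 30% with the same exclusion. None of the bands names an arm.
- **Analysis** (same section). The feasibility outcomes, with all three stop-go components among them, are analysed by "pooling the two randomised groups and presenting overall estimates with 95% CI". The intention-to-treat sentence that closes the section keeps patients in their randomised group, but it does not alter this pooling of the feasibility outcomes.
- **Consequence** (same section). Green on recruitment, adherence and drop-out together means a full trial with the protocol unchanged, unless the qualitative work gives a clear message. Any amber result means that the protocol is adapted first and a further feasibility or pilot study is considered.
- **Size** (Overview of study design): "Fifty participants will be randomised", "in a 1:1 ratio to the intervention or standard care for this population".
- **Burden.** The intervention arm has eight supervised sessions and 12 coaching calls (Overview of study design). The control arm has one advice call (Table 1, footnote).
- **Objective** (Aims and objectives): "Assess the acceptability of the intervention and the burden of trial participation on patients".

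**The concern.** Patients may leave the intervention arm because the programme is demanding. They may leave the control arm because, in an open-label trial, they know they did not get it. One average over both arms separates neither cause and hides any imbalance between them.

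Unequal loss is the retention problem that matters most for the definitive trial, because it can bias the comparison of self-reported fatigue. A feasibility study is the place to measure it. Here the pooled estimate is the only quantitative drop-out figure that the article commits to, and it feeds a decision rule. The point is therefore a stated choice for the primary outcome, not a detail left to the analysis plan.

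**Working it through.** The plan gives no expected drop-out rate and no formal sample size calculation, so there is no figure of its own to reproduce. The check applies its bands to possible counts.

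**Inputs.** From the document: 50 randomised 1:1; bands <15%, 15%–30% and >30%; green adherence >75%; adherence defined as at least 4 of 8 visits and at least 3 of 4 calls in weeks 9–12; stop-go analysis after the 24-week assessments. Assumed: exactly 25 per arm, no exclusions for disease activity, and adherence calculated over the 25 intervention patients.

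**1. Largest pooled count that is green.** 7/50 = 14% is green (exact 95% CI 5.8% to 26.7%). 8/50 = 16% is amber.

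**2. How seven drop-outs can be split.**

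| Intervention | Control | Pooled | Intervention-arm rate | Level in that arm |
|---|---|---|---|---|
| 4 | 3 | 14% | 4/25 = 16% | amber |
| 5 | 2 | 14% | 5/25 = 20% | amber |
| 6 | 1 | 14% | 6/25 = 24% | amber |
| 7 | 0 | 14% | 7/25 = 28% | amber |

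The exact 95% CI for 7/25 is 12.1% to 49.4%. Fisher's exact test of 7/25 against 0/25 gives p = 0.010.

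**3. Red level.** An arm is red from 8/25 = 32%. With no control loss this pools to 8/50 = 16%, which is amber.

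**4. Adherence as a backstop.** Green needs more than 75% of 25, so at least 19 adherent (19/25 = 76%). Suppose that early drop-outs count as non-adherent, which the article does not state.
- Six early drop-outs: at most (25 − 6)/25 = 76%, still green if everyone else adheres.
- Seven early drop-outs: at most (25 − 7)/25 = 72%, amber.
- Adherence is settled by week 12 and drop-out is assessed after week 24. A patient who withdraws in between may already count as adherent, so 28% loss can pass both criteria if at least one of the seven leaves late.

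**5. Probabilities at illustrative true rates of 25% (intervention) and 4% (control).** Let X ~ Bin(25, 0.25) and Y ~ Bin(25, 0.04), independent.
- Drop-out criterion alone: P(X + Y ≤ 7) = 0.56. For comparison, P(X ≤ 3), the intervention arm itself below 15%, is 0.10.
- Drop-out and adherence both green, with all intervention drop-outs early and a fraction q of the remaining patients non-adherent: sum P(X = x) P(Y = y) P(Bin(25 − x, 1 − q) ≥ 19) over x + y ≤ 7.

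| q | P(both green) |
|---|---|
| 0% | 0.50 |
| 5% | 0.36 |
| 10% | 0.24 |
| 15% | 0.14 |

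Late withdrawals would raise these figures.

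- Range for the drop-out criterion alone: 0.89 at true rates of 20% and 0%, falling to 0.12 at 35% and 8%.

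**The case against.** The strongest reply is that the protocol separates leaving the programme from leaving the study. A patient who stops exercising but still returns assessments is not a drop-out. Failure to tolerate the programme is the business of the adherence criterion, and acceptability is assessed by questionnaires and qualitative work. The burden of assessment (visits, nine questionnaires, a week of accelerometry at three time points) is the same in both arms. Green needs all three criteria and is also read against qualitative data, and reasons for non-completion are described. A split of 7 against 0 would be hard to overlook.

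Much of this stands, and it rules out three stronger readings that a reader might infer.
- *That 0.56 is the chance of an overall green light.* It is the chance for the drop-out criterion alone, at assumed rates. With adherence added it falls to between 0.14 and 0.50 under the assumptions in step 5, and recruitment must be green as well.
- *That a red-level arm can pass as green.* With 25 per arm and no exclusions it cannot. It takes a small imbalance, such as arms of 23 and 27 with all seven losses in the smaller arm (7/23 = 30.4%).
- *That the bands should therefore apply to the worse arm.* This has a real cost. If true drop-out is 10% in both arms, so that there is nothing to detect, the chance of green on drop-out falls from 0.88 (at most 7/50) to 0.58 (at most 3/25 in each arm). At 12% it falls from 0.75 to 0.42.

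The reply does not supply a by-arm estimate. The adherence criterion misses up to six early losses and any that come after week 12. The qualitative component is optional for patients, and the described reasons carry no threshold. Equal assessment burden does not make complete withdrawal equally likely when one arm also has 20 programme contacts and both arms know their allocation.

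**Conclusion.** The point holds in a limited form. The article fixes a single pooled drop-out estimate for the stop-go decision and commits to no by-arm figure. An intervention arm at amber level, 16% to 28%, can therefore be green on drop-out, and the adherence criterion catches only part of that loss. The risk is that a protocol with differential attrition goes forward unadapted because the imbalance was never put into numbers. Overall green despite such loss needs little other non-adherence, or withdrawals after week 12.

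The counts rest on 25 per arm with nobody excluded for disease activity. The probabilities rest on illustrative drop-out rates, since the document gives none, and on counting early drop-outs as non-adherent.

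**What to change.** Amend the pooling sentence in Study outcomes and data analysis so that:
1. drop-out is estimated in each arm, and as a between-arm difference, with 95% CIs, alongside the pooled rate;
2. the 15% and 30% bands stay on the pooled rate;
3. an intervention-arm rate at amber level, or a marked imbalance between arms, is weighed in the composite decision before the trial proceeds with the protocol unchanged.

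The same edit should say that adherence is calculated in the intervention arm only. Taken literally over all 50 patients it could not exceed 25/50 = 50%, which puts the 75% green level out of reach.

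The cost is a change of wording and one extra table, from data already collected. The drawback is imprecision in arms of 25, which is why the by-arm figures should guide judgement and not act as a hard worst-arm gate.
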